**Phase 1 Selection of Subjects**

The primary goal of the current study is to evaluate the feasibility, acceptability, recruitment and retention of Veterans with posttraumatic stress disorder (PTSD) for a treatment for smoking cessation that includes functional magnetic resonance imaging (fMRI)-guided repetitive transcranial magnetic stimulation (rTMS). For this feasibility study, we plan to screen 26 potential subjects, recruit/enroll 18 subjects (based on 8 not meeting eligibility criteria) and retain 14 subjects who complete at least 90% of all study procedures (based on a ~20% attrition rate). All human subjects in this project will be adult male and female Veterans. Potential participants will be recruited from the Durham Veterans Affairs Health Care System (DVAHCS). Study procedures will occur at both Duke University Medical Center (DUMC) and DVAHCS. Study inclusion and exclusion criteria are outlined below.

Phase 1 Inclusion/Exclusion Criteria:

| Subjects must meet **all** inclusion criteria: | Subjects must not have **any** exclusion criteria: |
| --- | --- |
| | - Is a US Veteran - Is between the ages of 18 and 75 (see Rossi et al., 2021) - Smokes an average of 10 cigarettes per day for the past 6 months, with carbon monoxide (CO) level > 6 ppm - Is willing to attempt smoking cessation - Meets DSM-5 criteria for current PTSD diagnosis - Speaks, reads and writes English - Currently an outpatient at DVAHCS - Is willing and able to participate in rTMS intervention, MRI and all required study visits - Is willing to sign a Duke consent for those portions of the study that occur at Duke. | | --- | | - Has previously received TMS - Has a current substance use disorder other than tobacco - Has a contraindication to TMS or MRI   - Personal or family history of a seizures or epilepsy   - History of neurological condition that increases the risk of seizures including stroke or transient ischemic attack, cerebral aneurysm, or severe traumatic brain injury from a penetrating head injury, loss of consciousness > 20 minutes at time of traumatic injury, requiring an anticonvulsant medication for seizures, and/or found to have encephalomalacia on baseline MRI   - Structural brain lesion, or prior brain surgery   - Ferromagnetic metal in head (including shrapnel)   - Implanted devices that may be affected by MRI or TMS (pacemaker, medication pump, cochlear implant, implanted deep brain stimulator)   - Is pregnant (to be determined at Duke) - Is unable to complete study procedures |

**Phase 2 Research Design and Methods**: The proposed study is a two-arm, parallel design, double-blinded, sham-controlled, randomized trial comparing active- vs sham- rTMS neuronavigated to a region on the post-central gyrus functionally connected to the insula in addition to evidence-based CBT for smoking cessation and NRT.

Overall Design: Fifty eligible participants will be randomized to one of 2 conditions: active-rTMS + CBT + NRT (n=25) or sham-rTMS + CBT + NRT (n=25). The full randomization sequence will be generated *a priori*. Participants will receive a baseline MRI scan, 5 daily neuronavigated active or sham rTMS treatments the week prior to their quit date, followed by a post-treatment MRI scan. In order to be able to use the fMRI results to inform placement of the TMS coils, there may be up to a two-week lag between the first MRI and the first TMS treatment session. All participants will receive 5 sessions of CBT for smoking cessation in which session 3 is designated as the quit date. All participants will also receive prescriptions of nicotine replacement in the form of 21 mg, 14 mg, and/or 7 mg patches and 2-4 mg nicotine gum or lozenges starting on the quit date and continuing for up to 90 days at individually tapered doses. All rTMS and MRI procedures will occur at Duke University Medical Center (DUMC). Participants will sign a Duke consent form and HIPAA authorization for those procedures.

We hypothesize that neuronavigated rTMS combined with CBT and NRT will be a safe, feasible, and effective method for smoking cessation in our study population. We anticipate being able to effectively recruit and retain eligible subjects in the study. Our primary feasibility endpoint will help determine successful completion of the study intervention and justification to continue this line of research. Recruitment will target enrolling 50 subjects, with a goal of 40 or more subjects completing at least 90% of all study procedures (>80% retention rate). We hypothesize that active- as compared to sham-rTMS will result in greater 7-day point prevalence abstinence rates (biochemically verified by exhaled carbon monoxide < 5 ppm) at end-of-treatment, and 3-month follow-up time points. We also hypothesize that active-rTMS will result in an increase in functional connectivity between the cortical rTMS target and the insula, therefore demonstrating target engagement. We also anticipate network-level differences in rsFC between active- vs sham-rTMS groups. We will also monitor levels of nicotine dependence, cravings, withdrawal, prolonged abstinence, psychiatric symptoms related to PTSD and depression, and alcohol use.

**The primary outcome** to be evaluated in the feasibility aim will be recruitment and retention of subjects, with a target enrollment of 50 subjects and 80% retention rate (i.e., 40 completers). For the efficacy aim, we will estimate the effect size by evaluating 7-day point prevalence at the end-of-treatment, and 3-months post-quit date using previously established methods of self-reported abstinence and bioverification. For the target engagement aim, we will evaluate functional connectivitybetween the rTMS target on sensorimotor cortex and right posterior insula.

**Secondary/exploratory outcomes** will be network-level changes on rsFC using the right posterior insula as a region-of-interest; levels of nicotine dependence using the Fagerström Test for Nicotine Dependence (FTND); nicotine cravings using the Brief Questionnaire of Smoking Urges; nicotine withdrawal on the Minnesota Nicotine Withdrawal Scale-Revised (MNWS-R); PTSD symptoms as measured by the PCL-5, depressive symptoms as measured by the BDI-II; alcohol use as measured by the alcohol use disorders identification test-consumption (AUDIT-C) screening tool; and illicit substance use as measured by the drug abuse screening test (DAST).

**Phase 2 Study Procedures**

Screening Visit: These study procedures are similar to Phase 1 of the project. Once considered eligible to participate in the study, participants will be randomized 1:1 to receive either active rTMS or sham rTMS. Participants will remain blinded to study condition throughout the study. [name] and [name] will also remain blinded to study condition.

Medical Screening: These study procedures are similar to Phase 1 of the project. However, in lieu of one screening session, we will divide the screen tasks between two visits. Diagnostic interviews will be completed at the first visit, and questionnaires and CO readings will be completed at the second.

Biochemical Verification of Abstinence: Participants will provide exhaled breath carbon monoxide (CO) levels at baseline, quit date, end-of-treatment, and at 3-month follow-up visit. We will use a standardized cutoff value of < 5 ppm. In addition, at the post-treatment and 3-month follow-up visit, urinary cotinine will also be collected for more comprehensive bioverification for those participants who are no longer using NRT. Urine samples collected will be sent to LabCorp for analysis.

DUMC Study Procedures: MRI procedures are identical to Phase 1 MRI procedures. MagVenture’s MagPro X100 will be used for rTMS procedures. rTMS parameters will be updated from Phase 1 to Phase 2 due to advances in the field and Phase 1 data. Phase 1 will be 5 daily rTMS sessions of 1 Hz 960 pulses for 16 minutes each. Phase 2 will be 5 days of rTMS treatments twice daily using patterned rTMS, intermittent theta burst stimulation (iTBS; 3-pulse 50-Hz bursts at 5-Hz for 2-s trains, with trains every 10 s) 1800 pulses at 90% rMT for 9 minutes each separated by at least 50 minutes. Active- or sham-rTMS will be determined by utilizing a subject-specific code recognized by the TMS device as active or sham, which then instructs staff as to which side of the TMS coil to use. The Magventure B65 A/P coil has identical sides, but the computer will know which side to use based on each participant code. A cue provocation procedure to induce nicotine cravings will be conducted prior to rTMS treatments using a video of smoking-related images as well as instructions for handling of a cigarette and lighter. Following the last rTMS session, a second fMRI scan (post-rTMS fMRI) will be conducted at least 1 hour and up to 24 hours later.

Additional Study Interventions: Smoking cessation counseling and nicotine replacement therapies are identical to those offered in Phase 1. Participants will be offered NRT for at least 60 days.

Measures: The following measures will be obtained to ensure subject eligibility, determine whether subjects are willing to complete these questionnaires, and to characterize the sample for the CDA-2 pilot. Where possible, participants will complete coded study measures via Qualtrics using their own electronic devices (e.g., smart phones, computers, tablets). If a participant does not have a device available, they will be allowed to complete the measures by mail or in person. All data will be stored at VA Qualtrics, which is FedRAMP approved for collection and storage of VA PHI and VA sensitive information.

Subject Sociodemographic and Clinical Background Variables: Participants will complete a background sociodemographic and military service measure at screening to characterize the subject sample.

Diagnostic Assessment and Psychiatric Measures: A thorough evaluation for psychiatric conditions will be completed using the Structured Clinical Interview for DSM-5 (SCID-5; First et al, 2015). To ensure subjects meet study criteria for a PTSD diagnosis, the Clinician Administered PTSD Scale for DSM-5 (CAPS-5), a semi-structured interview considered to be the “gold standard” for PTSD diagnostic assessment (Weathers et al, 2015), will be used. PTSD symptoms will be monitored using the past-month version of the PCL-5, a 20-item self-report measure successfully used in Veterans for monitoring symptom change with treatment (Blevins et al, 2015; Bovin et al, 2015). The BDI-II will be used to monitor depressive symptoms (Beck et al, 1996), illicit substance use will be monitored using past-year and past month versions of the DAST (Bohn et al, 1991), and alcohol use will be tracked using the 3-item AUDIT-C (Bush et al, 1998).

Tobacco-Related Measures: Tobacco-related measures will include the FTND (Heatherton et al, 1991), the MNWS-R (Hughes, 2012), the Brief Questionnaire on Smoking Urges, and a 100-point scale on Smoking Urges. These scales will characterize levels of dependence on nicotine include number of cigarettes smoked daily, withdrawal, and cravings. At baseline, participants will participate in a cue provocation procedure to induce (and measure) nicotine cravings. The procedure includes watching a brief video with smoking-related images, with instructions for the participant to handle a cigarette and lighter. At three time points, we will ask participants about their motivation to quit smoking and confidence to stop smoking long term. The question regarding motivation to quit will only be asked of those participants who are still smoking at posttreatment and follow-up. We will also monitor tobacco use with a calendar for timeline follow back.

rTMS-Related Measures: To assess Veterans’ perceived credibility and expectancy of TMS procedures, the Credibility/Expectancy Questionnaire (Devilly & Borkovec, 2000) will be administered at baseline and post-rTMS/quit date. To determine Veterans’ acceptability of the intervention, we will measure a patient satisfaction questionnaire tailored to this study’s treatment aims, administered at the post-rTMS/quit date and 2-week follow-up assessments. To determine Veterans’ tolerability of the intervention, a brief TMS side effect rating scale will be administered at the post-rTMS/quit date and 2-week follow-up assessments. We will also assess subjective distress using the Subjective Units of Distress Scale (SUDS).

Table 2. Measures Administered in Phase 2 at Major Study Time Points

| **Measure** | **Time Point** | | | |
| --- | --- | --- | --- | --- |
| **Baseline** | **Quit Date** | **End-of-treatment** | **3-Month**  **Follow-up** |
| Sociodemographic and Military Background | X |  |  |  |
| MRI Safety Screening | X |  |  |  |
| TMS Safety Screening | X |  |  |  |
| OSU-TBI | X |  |  |  |
| ***Diagnostic Assessment and Psychiatric Measures*** | | | | |
| SCID-5 | X |  |  |  |
| CAPS-5 (past month) | X |  |  |  |
| PCL-5 (past month) | X | X | X | X |
| IDS-SR | X | X | X | X |
| AUDIT-C | X | X | X | X |
| DAST (past year) | X |  |  |  |
| DAST (past month) | X | X | X | X |
| ***Tobacco-Related Measures and Bioverification*** | | | | |
| FTND | X | X | X | X |
| MNWS-R | X | X | X | X |
| Brief Questionnaire on Smoking Urges | X | X | X | X |
| *Exhaled CO* | X | X | X | X |
| Motivation to quit and confidence to stay quit items | X |  |  | X |
| Cue Provocation/Cravings Measure | X |  |  |  |
| *Urinary Cotinine* |  |  |  | X |
| ***rTMS-Related Measures*** | | | | |
| Credibility/Expectancy Questionnaire | X | X |  |  |
| TMS Side Effects Scale |  | X | X | X |
| Acceptability Questionnaire |  | X | X | X |
| Treatment Allocation Guess |  | X | X | X |
| MRI = magnetic resonance imaging; TMS = transcranial magnetic stimulation; OSU-TBI = Ohio State University-Traumatic Brain Injury Identification Method-Short Form; Structured Clinical Interview for DSM-5 = SCID-5; Clinician Administered PTSD Scale for DSM-5 = CAPS-5; PTSD Checklist for DSM-5 = PCL-5; Inventory of Depressive Symptomatology-Self Report = IDS-SR; Alcohol Use Disorders Identification Test Consumption Screening Tool = AUDIT-C; Fagerström Test of Nicotine Dependence = FTND; Minnesota Nicotine Withdrawal Scale-Revised = MNWS-RS; DAST = Drug Abuse Screening Tool | | | | |

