Diagnostic Assessment and Psychiatric Measures: A thorough evaluation for psychiatric conditions will be completed using the Structured Clinical Interview for DSM-5 (SCID-5; First et al, 2015). To ensure subjects meet study criteria for a PTSD diagnosis, the Clinician Administered PTSD Scale for DSM-5 (CAPS-5), a semi-structured interview considered to be the “gold standard” for PTSD diagnostic assessment (Weathers et al, 2015), will be used. PTSD symptoms will be monitored using the past-month and past-week versions of the PCL-5, a 20-item self-report measure successfully used in Veterans for monitoring symptom change with treatment (Blevins et al, 2015; Bovin et al, 2015). The Inventory of Depressive Symptomatology – Self Report (IDS-SR; Rush, Carmody, & Reimitz. 2006) will be used to monitor depressive symptoms, illicit substance use will be monitored using past-year and past month versions of the DAST (Bohn et al, 1991), and alcohol use will be tracked using the 3-item AUDIT-C (Bush et al, 1998).

Tobacco-Related Measures: Tobacco-related measures will include the FTND (Heatherton et al, 1991), the MNWS-R (Hughes, 2012), the Brief Questionnaire on Smoking Urges, and a 100-point scale on Smoking Urges. These scales will characterize levels of dependence on nicotine include number of cigarettes smoked daily, withdrawal, and cravings. We will also monitor tobacco use with a calendar for timeline follow back.

rTMS-Related Measures: To assess Veterans’ perceived credibility and expectancy of TMS procedures, the Credibility/Expectancy Questionnaire (Devilly & Borkovec, 2000) will be administered at baseline and post-rTMS/quit date. To determine Veterans’ acceptability of the intervention, we will measure a patient satisfaction questionnaire tailored to this study’s treatment aims, administered at the post-rTMS/quit date and 2-week follow-up assessments. To determine Veterans’ tolerability of the intervention, a brief TMS side effect rating scale will be administered at the post-rTMS/quit date and 2-week follow-up assessments. We will also assess subjective distress using the Subjective Units of Distress Scale (SUDS).

Table 1. Measures Administered in Phase 1 at Major Study Time Points

| **Measure** | **Time Point** | | |
| --- | --- | --- | --- |
| **Baseline** | **Post-rTMS / Quit Date** | **2-week Follow-Up** |
| Sociodemographic and Military Background | X |  |  |
| **Diagnostic Assessment and Psychiatric Measures** | | | |
| SCID-5 | X |  |  |

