**Phase 1 and Phase 2 Study Interventions**

Smoking Cessation Counseling: [name] laboratory will provide trained therapists to administer five weekly evidence-based smoking cessation counseling sessions. Cognitive behavioral therapy (CBT) for smoking cessation will be provided by a therapist who has been trained in CBT administration. All therapists are rigorously trained and receive ongoing supervision. The counseling sessions will be done via video or telephone.

Smoking Cessation Pharmacotherapy: All eligible participants will be prescribed NRT of at least one nicotine rescue method (e.g., patch, gum, inhaler) at the medical screening evaluation and continued as needed during the duration of the study. NRT will be prescribed by the study physician and mentor, [name]., Ph.D. [name] will write the prescriptions and work with participants' primary care physician or psychiatrist to discuss any contraindications. The applicant, [name]., will serve as a back-up prescriber in the event of [name] absence. If no contact from the primary care physician can be made, the participants' health information will be evaluated by the study physician, who will determine medical clearance to participate in the trial. Neither varenicline nor bupropion will be prescribed due to the potential for increased risk of seizures during rTMS (FDA, 2015; Little and Ebbert, 2016).

Because the study procedures are not targeting PTSD symptoms, participants will be informed during the informed consent process that they will not be asked to stop any ongoing PTSD treatments, nor will they be asked to refrain from beginning new treatments.

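### In Phase 2 the PCL-5 is given only with past-month recall, so the quit-date score mostly describes the weeks before rTMS began

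*Protocol*

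**What the plan says.** Under Phase 2 Study Procedures (Diagnostic Assessment and Psychiatric Measures) the protocol states that "PTSD symptoms will be monitored using the past-month version of the PCL-5". The Table 2 row agrees: "PCL-5 (past month) | X | X | X | X". The four columns are baseline, quit date, end-of-treatment and 3-month follow-up, and no shorter-recall version appears anywhere in Phase 2. The drug-use scale follows the same pattern after baseline: "DAST (past month) | X | X | X | X". The Phase 2 outcome list names both scales as secondary/exploratory.

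On timing, the Phase 2 Overall Design gives participants "5 daily neuronavigated active or sham rTMS treatments the week prior to their quit date". It adds that "All participants will receive 5 sessions of CBT for smoking cessation in which session 3 is designated as the quit date". The interventions section describes "five weekly evidence-based smoking cessation counseling sessions", which puts session 5 about 14 days after the quit date. No section dates the end-of-treatment visit.

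The Phase 1 text differs: "PTSD symptoms will be monitored using the past-month and past-week versions of the PCL-5". Table 1, however, lists only the past-month version.

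**The concern.** A symptom scale can register a change only to the extent that its recall period lies after the change could have begun. Here the first assessment after rTMS comes about a week after stimulation started, while the form asks about a month. Most of what the participant is asked to recall happened before the first session. Some of it may also have been recalled at baseline, if the two visits are less than a month apart.

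At stake is the meaning of the early PTSD scores. The protocol cites the PCL-5 as suited to tracking change during treatment, its background links quitting with fewer PTSD symptoms, and its risk section lists mood and sleep disturbance from withdrawal. Phase 2 is also meant to inform a later full trial. A flat PCL-5 from baseline to quit date could be read as no early effect of rTMS when the recall window would produce much of that flatness by itself. An analysis plan cannot repair this, because past-week scores cannot be recovered from a past-month form.

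**Working it through.** The protocol gives no sample size, power or effect size for the PCL-5, so there is no figure to reproduce. The check is calendar arithmetic.

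**Inputs**
- Recall length R: past month, taken as 30 days (range 28-31).
- Days from first rTMS session to quit date, s: 5 to 7, because five daily treatment days fall in the preceding week.
- Days from quit date to end-of-treatment, g: not stated. Assumed 14 (CBT session 5), with 21 as an alternative.
- 3-month visit: about 90 days after the quit date.

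**Formula**

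Share of the window before the first session = max(0, R − d)/R, where d is the number of days from the first session to the assessment.

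| Visit | d (days) | Pre-rTMS share, R = 30 | Range, R = 28-31 |
|---|---|---|---|
| Quit date | 5 to 7 | 25/30 = 83% to 23/30 = 77% | 75-84% |
| End-of-treatment, g = 14 | 19 to 21 | 11/30 = 37% to 9/30 = 30% | 25-39% |
| End-of-treatment, g = 21 | 26 to 28 | 4/30 = 13% to 2/30 = 7% | 0-16% |
| 3 months | 95 to 97 | 0% | 0% |

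The quit-date result is robust. Even if the first session were 10 days before quitting, the share would be 20/30 = 67% (64-68% for R = 28-31).

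**Attenuation**

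Suppose recalled days count equally and an effect starts at the first session and stays constant. The visible fraction is then 1 minus the share above: 5/30 to 7/30 (17-23%) at the quit date and 19/30 to 21/30 (63-70%) at end-of-treatment with g = 14. The documents state neither assumption, so these fractions are illustrative. The window shares do not depend on them.

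**Past-week recall at the quit date**

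The pre-rTMS share becomes max(0, 7 − s)/7: 0% if the first session was 7 days earlier and 2/7 = 29% if it was 5 days earlier.

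**Coverage after quitting (quit date = day 0)**
- Past-week at the quit date covers days −7 to −1.
- Past-week at end-of-treatment on day 14 covers days 7 to 13, so past-week forms alone leave days 0 to 6 in no window at these two visits.
- Past-month at day 14 covers days −16 to 13. That includes every day since quitting, although 16/30 = 53% of the window precedes quitting.

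The two versions therefore complement each other at end-of-treatment, and the past-month form should stay there.

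**The case against.** The strongest counter-argument is that little depends on these scores. The PCL-5 sits in a long secondary/exploratory list. The interventions section says PTSD is not what the procedures aim to treat, and the Phase 1 analysis text anticipates no movement in psychiatric symptoms. The protocol also gives eligibility, willingness to complete the forms and sample description as purposes of the measures. Both arms share the schedule, so the window shrinks any difference and does not favour an arm. Acute deterioration is covered separately by real-time adverse-event monitoring and a psychiatric-emergency procedure. Phase 2 is also consistent with itself, since text and Table 2 both say past-month. All of this stands and sets the priority low. It does not change what the quit-date score measures.

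A reader might infer several stronger things that the documents do not support:
- **That neither early score can show any change.** At end-of-treatment most of the window lies after rTMS began, so attenuation there is partial, and its size depends on an undated visit.
- **That the recall period hides an effect of quitting at the quit date.** No recall version could show one, because no post-quit day has passed.
- **That past-week should replace past-month at end-of-treatment.** That would leave the first week of abstinence unobserved.
- **That the DAST needs a new version.** The same overlap exists, but the protocol names no shorter-recall DAST and plans no specific analysis of DAST change at the quit date.

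**Conclusion.** The point holds for the quit-date PCL-5. About 77-83% of a 30-day look-back precedes the first rTMS session, so that score is mainly a pre-treatment measure and early rTMS-related change in it is strongly attenuated. This rests on a past month of about 30 days and a first session 5 to 7 days before quitting. Other plausible values move the share but leave it above 60%.

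The end-of-treatment score is affected to a lesser and uncertain degree, depending on whether the visit falls nearer 14 or 21 days after quitting. The 3-month score is not affected. Any statement about how far an effect shrinks also needs equal weighting of recalled days and an immediate, constant effect, so it should be offered only as an illustration.

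This is an inexpensive improvement to an exploratory outcome. It does not threaten the trial's main conclusions.

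**What to change.** In the Phase 2 measures text and Table 2:
- Add the past-week PCL-5 at baseline, quit date, end-of-treatment and 3 months, so that change is measured like for like.
- Keep the past-month PCL-5 at baseline (alongside the past-month CAPS-5), at end-of-treatment (so that the first week after quitting stays covered) and at 3 months. Drop it at the quit date.
- State that the past-month DAST at the quit date is not to be interpreted as a post-rTMS measure. No new DAST version is needed.

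Separately, reconcile the Phase 1 text, which names both PCL-5 versions, with Table 1, which lists only past-month.

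The cost is a small amendment and one additional 20-item form at baseline, end-of-treatment and 3 months, a few minutes each. At the quit date one form replaces another, so the burden there is unchanged, but the past-month score at that visit is lost.

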**Phase 1 and 2 Risk/Benefit Assessment**

**Potential Risks**

Overall, the risks to subjects are low in light of the potential benefits to them for participating in the study, including quitting smoking. Participants may receive satisfaction from contributing to the progress of scientific research.

Study-related serious adverse events are not expected but will be closely monitored and will be reported in accordance with VA, DUMC, and FDA policy.

Study Assessments: Regarding completion of study measures and structured interviews, there is a risk of discomfort or distress in answering questions, especially questions related to traumatic experiences. However, distress and discomfort related to these study activities are usually temporary and well-tolerated. Previous studies in our laboratory that have included trauma- and PTSD-related questionnaires, interviews, and treatment have had no greater than expected adverse events related to study participation. Every effort will be made to make the environment comfortable and supportive during assessment procedures. Risks also include discomfort related to quitting smoking. Quitting smoking will cause nicotine withdrawal that may lead to headaches, nausea, irritability, weight gain, difficulty concentrating, poor sleep, increased appetite, anxious or depressed mood, and craving for cigarettes. There are risks associated with the use of NRT. Minimal risks associated with wearing a nicotine patch include skin irritation, dizziness, lightheadedness, increased heart rate or blood pressure, nausea or vomiting. Inherent to any research, there is also a potential risk associated with the loss of confidentiality of study data.

Please note, risks associated with study procedures that occur at DUMC are described in the Duke IRB protocol and informed consent document.

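### The Phase 2 side-effect scale has no baseline, treatment-week or early-discontinuation rating, so within an arm stimulation effects cannot be cleanly told from pre-existing or quitting symptoms

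*Protocol*

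**What the plan says.** The rTMS-Related Measures paragraph under Phase 2 Study Procedures makes a side-effect scale the means of judging tolerability, and says that "a brief TMS side effect rating scale will be administered at the post-rTMS/quit date and 2-week follow-up assessments". Table 2 (Measures Administered in Phase 2) has a row for the "TMS Side Effects Scale" with an empty baseline cell and marks at quit date, end-of-treatment and 3 months.

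All stimulation comes before the first of these ratings. The Phase 2 Overall Design paragraph gives "5 daily neuronavigated active or sham rTMS treatments the week prior to their quit date", with nicotine replacement starting on the quit date. The DUMC Study Procedures paragraph describes the regimen differently: "Phase 2 will be 5 days of rTMS treatments twice daily using patterned rTMS, intermittent theta burst stimulation".

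Potential Risks lists the symptoms to expect from stopping smoking: "Quitting smoking will cause nicotine withdrawal that may lead to headaches, nausea, irritability", among others. For the nicotine patch it lists "skin irritation, dizziness, lightheadedness, increased heart rate or blood pressure, nausea or vomiting".

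The section on withdrawal of participants does not mention a side-effect rating when someone leaves treatment early.

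**The concern.** Phase 2 hypothesises that the intervention is safe and feasible, and it uses a stimulation regimen that Phase 1 did not use. Tolerability ratings from Phase 1 therefore cannot stand in for Phase 2 ratings. The schedule leaves three gaps in the one structured tool:

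- **No baseline.** A headache or poor concentration reported at the quit date may have been there before the first pulse.
- **No rating between the first session and the quit date.** The first rating is taken on the day that two other sources of similar symptoms begin.
- **No rating at early discontinuation.** Those who stop because of discomfort tell the most about tolerability, and they are the ones most easily left without a rating.

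The stake is how well the tolerability data describe the Phase 2 regimen for the planned larger trial. No primary or secondary outcome of Phase 2 is affected.

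**Working it through.** **1. Text against table.** The Phase 2 sentence repeats the Phase 1 sentence, where a two-week visit does exist in Table 1. Table 2 has no such column. The quit date is session 3 of 5 weekly counselling sessions, so session 5 falls 5 − 3 = 2 weeks later. End-of-treatment may therefore be the visit meant. Even so, the table has a 3-month rating that the text omits. Both sources agree that there is no baseline rating and that the quit date is first.

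**2. Exposure before the first rating.** By DUMC Study Procedures: 5 days × 2 = 10 sessions, and 10 × 1,800 = 18,000 pulses. Phase 1 was 5 × 960 = 4,800 pulses. The Overall Design paragraph can be read as one session a day. The two passages must be reconciled, but on either reading the whole course precedes the first rating.

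**3. The plan's own figure.** Data Analysis and Statistical Considerations states 50 enrolled, 40 retained and 20% attrition: 40 / (1 − 0.20) = 50. This reproduces. The protocol gives no tolerability rate, threshold or power, so the rates in steps 4 and 5 are assumptions.

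**4. What the sham comparison can recover.** Let b be the share in each arm with a symptom from quitting or background, and r the share in whom active stimulation causes it, independently of b. Assume that sham causes none.

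- Active rate = 1 − (1 − b)(1 − r); sham rate = b.
- Example, b = 0.30 and r = 0.30: active = 1 − 0.70 × 0.70 = 0.51; difference = 0.51 − 0.30 = 0.21.
- Recovered effect = 0.21 / (1 − 0.30) = 0.30 = r.
- 95% half-width at 25 per arm = 1.96 × √[(0.51 × 0.49 + 0.30 × 0.70) / 25] = 0.266.

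| b | r | Difference | Half-width, 25 per arm | Half-width, 20 per arm | Power, 25 / 20 per arm |
|---|---|---|---|---|---|
| 0.1 | 0.1 | 0.09 | 0.194 | 0.216 | 14% / 12% |
| 0.1 | 0.3 | 0.27 | 0.223 | 0.249 | 62% / 52% |
| 0.3 | 0.1 | 0.07 | 0.261 | 0.292 | 8% / 7% |
| 0.3 | 0.3 | 0.21 | 0.266 | 0.297 | 32% / 27% |
| 0.5 | 0.1 | 0.05 | 0.276 | 0.309 | 5% / 5% |
| 0.5 | 0.3 | 0.15 | 0.271 | 0.303 | 19% / 16% |

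The comparison can recover the effect of active over sham stimulation, but only in the second row does the expected difference exceed the half-width. A larger shared background also shrinks the absolute difference: at r = 0.3 it falls from 0.27 to 0.15 as b rises from 0.1 to 0.5.

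**5. Unrated early stoppers.** Assume that 20% of those rated report a given side effect.

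- 5 of 25 in an arm unrated: observed 4/20 = 20%; possible range 4/25 = 16% to (4 + 5)/25 = 36%.
- All 10 losses in one arm: observed 3/15 = 20%; possible range 3/25 = 12% to (3 + 10)/25 = 52%.

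These are outer bounds. The 20% counts anyone who completes less than 90% of all procedures, and many of those could still be rated at the quit date.

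**The case against.** A reader might infer that side effects of stimulation cannot be separated from quitting at all, or that early stoppers vanish from the safety data. The protocol does not support either reading.

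- Both arms have the same quit date, counselling and nicotine replacement, so quitting symptoms are shared and the randomised comparison addresses them. This stands. It does not describe tolerability within the active arm or isolate effects that sham itself causes, and it is imprecise.
- The MNWS-R rates withdrawal separately, from baseline onward. This stands, but it does not say which source produced an item on the side-effect scale, and that scale has no baseline of its own.
- Adverse events are monitored in real time with onset, resolution, severity and relatedness, so events in the treatment week can be dated. This stands. It is event reporting, and the protocol does not state that every participant is asked the same questions each day.
- The quit-date rating follows directly on the treatment week, when withdrawal and nicotine replacement are only starting, so mixing is smallest there. The recall window is not stated and might cover the treatment week.
- SUDS is named for Phase 2, and in Phase 1 it is taken during TMS procedures. For Phase 2 it has no time point and no row in Table 2, and it measures distress.
- Stopping rTMS need not mean missing the quit-date rating, since questionnaires can be completed electronically or by mail.
- Potential Risks refers to a separate Duke protocol for procedures done there. That document is not at hand and may contain session checks.

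**Conclusion.** The point holds in a limited form. The scale that the protocol names for tolerability has no baseline, no rating in the rTMS week and none at early discontinuation. Within an arm, therefore, stimulation side effects cannot be cleanly distinguished from pre-existing or quitting symptoms, and some early stoppers may have no rating on this scale. The gap concerns the scale and does not extend to all safety data.

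The protocol gives no rates from which to size the effect. Under the assumed ranges (b from 0.1 to 0.5, r from 0.1 to 0.3, independence, no sham effects), the half-width is 0.19 to 0.28 at 25 per arm and 0.22 to 0.31 at 20 per arm, with power of 5% to 62%. The sham comparison alone is thus a weak substitute for a rating taken before quitting. Tolerability is not a listed Phase 2 primary or secondary outcome and has no threshold, so this is a cheap improvement and does not threaten the trial's main conclusions. It would fall away in large part if the Duke protocol already collects structured ratings at each session.

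**What to change.** In the Phase 2 rTMS-Related Measures paragraph and in Table 2:

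- Add the existing side-effect scale at baseline and on the rTMS days; at minimum, give it after the last session and before the quit date.
- Obtain it from anyone who stops rTMS early, remotely if needed.
- Summarise tolerability by arm on these pre-quit ratings. Keep the quit-date, end-of-treatment and 3-month ratings as follow-up; none needs to be dropped.
- Reconcile the two-week visit in the text with the Table 2 columns, and state when SUDS is taken in Phase 2.
- Reconcile the two descriptions of the number of daily sessions.
- If the Duke protocol already holds per-session ratings, cite them in Table 2 and use them.

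The cost is a schedule amendment and a few minutes of extra participant burden per rTMS day, at visits that already take place.
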